### Statistical Analyses

Response frequency, proportions, and means will be calculated. Means and standard deviations, medians and interquartile ranges, distributions, frequencies, and percentages will characterize the data. Comparisons on demographics (ie, age, marital status) will be done using chi-square tests, *t* tests, and correlations, with 2-tailed *P*=.05. The changes from baseline to all postbaseline visits until week 24 in steps per day will be assessed. The model includes response data from all postbaseline visits with no imputation for missing data, as the model assumes missingness at random. The step counts at baseline are included as a fixed factor in the model. An unstructured covariance structure is assumed, and the denominator degrees of freedom is computed using the Kenward-Roger method. In case the model will not converge with the unstructured covariance structure, the heterogeneous compound symmetry and the heterogeneous Toeplitz structure is used instead (in that order). The least-squares mean estimates for the mean change from baseline to week 24 as well as the difference in the estimates at 12 weeks is displayed with their corresponding standard errors, *P* values, and 95% CI. The characteristics of the dropouts and/or noncompliant individuals are intensively examined to shed light on the potential weaknesses of the MobileMen app (differential dropout overall or within certain subgroups) and assumptions about missingness in the estimates. The evaluation of the app will include its impact using the pre-post data. The examination of the correlation matrices along with the mean changes will inform whether the variables appear to move similarly in both arms and how the interventions are working.

To identify possible mediating constructs, we plan to assess preintervention and postintervention SDT motivation and self-efficacy for PA. The selected mediation variables will be assessed using PROC CAUSALMED, which provides estimates of direct, indirect, and total effects. We will be able to judge if mediation is occurring, and if so, the strength and direction of the mediation effect. Since this study may not have an adequate sample size to power mediation effectively, this analysis will be primarily used to estimate the potential effect in a larger sample for future trials.

App utilization data will be examined to understand the acceptability and intensity of the interactions with MobileMen via several criteria, including but not limited to logins, notifications sent and received, number of activities inputted, badges earned, tips read, number of health parameters inputted, competitions competed in, and incentives earned. Complier average causal effect models will be used to examine the intensity of the intervention app utilization [73].

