**Methods:**

We will recruit a sample of “low active” (accumulating <7500 steps per day) African American men (n=100) aged >30 years from Baton Rouge, Louisiana, and the surrounding communities. All participants are given a Fitbit Charge 6 wearable activity tracker to assess daily PA and steps and are randomized to either the MobileMen intervention app or the comparator app, which is a commercially available PA tracking app called Stridekick. The Stridekick app has features similar to those in the MobileMen app but was not intentionally designed for African American men. The intervention period is 6 months during which participants will interact with their assigned mobile app. MobileMen includes features such as digital badges earned for PA; tangible prizes like exercise equipment; challenges among participants; goal setting; nutrition; PA; and behavior change educational information in text, audio, and video formats. Participants will complete assessments at baseline and at 6 months post randomization. Assessments include objective measurements of daily steps and minutes of moderate to vigorous PA, quality of life, dietary measures, self-efficacy for fruit and vegetable consumption and PA, and autonomous motivation for PA.

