At the start of this remote or in person visit, study staff evaluate the Fitbit wear compliance. Participants who did not wear the Fitbit for at least 3 weekdays and 1 weekend day are required to rewear the device. Participants who self-report <60 minutes of moderate to vigorous PA on the International Physical Activity Questionnaire are eligible. Eligible participants are randomized to one of the 2 conditions, the MobileMen intervention group or the Stridekick comparator group, as directed by the next assignment letter contained in a randomized sequence of sealed and numbered envelopes. Using a computerized pseudorandom number generator, the statistician determines the randomization order in advance. The study coordinator reveals the randomization after the participant is deemed eligible. Project staff assist each participant in downloading the designated (MobileMen or Stridekick) app onto their smartphone, provide an app orientation, and assist in app navigation.

### Study Visit 3

At the conclusion of the 6-month intervention, participants complete all follow-up assessments (except for the Physical Activity Readiness Questionnaire for Everyone and demographic questionnaires) by using the same protocols as in study visit 1. Participants in both groups also complete additional measures such as a survey to assess their satisfaction with the mobile app and the System Usability Scale, a validated 10-item measure that provides a global view of the subjective usability for technology, to assess the app’s usability [70]. Participants also complete a brief interview with the study staff to collect feedback regarding suggestions for app improvement and users’ impressions of the app content.

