### Outcome Measures

#### Primary Outcomes

The primary outcome measure for this study is change in step counts derived from the Fitbit collected before the intervention (week 0) and after the intervention (week 24).

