#### Secondary Outcomes

Time spent in moderate to vigorous PA, also derived from the Fitbit preintervention and postintervention data, is a secondary outcome measure. Other secondary outcomes include changes in body weight, blood pressure, quality of life, and healthy eating index score. Daily PA engagement assessed with Fitbit Charge 6 is another secondary outcome measure. Using the Fitbit application programming interface, study staff will access participant daily steps, time spent engaging in PA, number of PA bouts, and minutes spent in each Fitbit-defined heart rate zone. Although Fitbit’s thresholds and algorithms are proprietary, research indicates that minutes categorized in Fitbit data as “active” (fairly active plus very active) generally correspond to what we consider moderate to vigorous PA [71-73]. Usability (using the System Usability Scale) and overall satisfaction with the MobileMen app are the additional secondary outcomes.

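### The reported difference in step estimates is placed at 12 weeks, not at the week-24 primary time point, and no week-24 between-arm difference is stated

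*Protocol article*

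**What the plan says.** Under Primary Outcomes, the protocol article defines the primary measure as "change in step counts derived from the Fitbit collected before the intervention (week 0) and after the intervention (week 24"). The Methods part of the Abstract gives the schedule: "Participants will complete assessments at baseline and at 6 months post randomization". It counts step data among those assessments: "Assessments include objective measurements of daily steps and minutes of moderate to vigorous PA". Study Visit 3 is the only visit after randomization: "At the conclusion of the 6-month intervention, participants complete all follow-up assessments".

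The last paragraph of the Introduction states the hypothesis as a comparison of MobileMen with Stridekick. It gives no time point.

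Statistical Analyses then describes a model of change in steps: "The changes from baseline to all postbaseline visits until week 24 in steps per day will be assessed". On what will be reported, it says that the "mean change from baseline to week 24 as well as the difference in the estimates at 12 weeks is displayed", with standard errors, P values and 95% confidence intervals.

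Under Secondary Outcomes, the article adds that through the Fitbit interface "study staff will access participant daily steps, time spent engaging in PA, number of PA bouts" and further activity measures. It lists daily activity from the device as a secondary outcome.

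**The concern.** In a two-arm trial with a change-from-baseline endpoint, the sentence listing the displayed estimates should contain the between-arm difference at the primary time point. Here it attaches week 24 to the mean changes and 12 weeks to the difference. Read literally, it gives week-24 mean changes together with a difference at a time that the outcome definition and the visit schedule do not contain.

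This sentence tells a reader of the eventual report which number is the trial's main result. As it stands, a report giving a week-12 difference would match the analysis section but not the primary outcome. A report giving the week-24 difference would match the outcome but not the analysis section.

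**Working it through.** **Time points, set side by side**

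| Place in the protocol article | Time point | Content |
|---|---|---|
| Introduction, last paragraph | none given | MobileMen versus Stridekick |
| Abstract, Methods | baseline and 6 months | assessments, including objective steps |
| Study Visit 3 | end of the 6-month intervention | all follow-up assessments |
| Primary Outcomes | week 0 and week 24 | change in Fitbit steps |
| Secondary Outcomes | daily | Fitbit steps and activity |
| Statistical Analyses, mean changes | week 24 | least-squares means |
| Statistical Analyses, difference | 12 weeks | difference in the estimates |

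Taking week 24 and 6 months as the same occasion, there is one scheduled assessment after randomization at week 24 and none at week 12. No row gives a between-arm difference at week 24.

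**Can the 12-week reference be reconciled with the rest?** There are two ways to try.

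1. *It is a slip for 24 weeks.* This fits the outcome definition and the schedule. The article does not say so.
2. *It is a real interim time point from daily Fitbit data.* The model description speaks of several postbaseline visits and an unstructured covariance, which suggests repeated measurements after baseline. But the schedule has only one such visit, the daily data are a secondary outcome, and no week-12 window is defined.

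The text does not decide between the two. Under either, the week-24 between-arm difference is still unstated.

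**Does the time point affect the sample size?** The inputs in Sample Size and Power Calculation are 50 per arm, an SD of 2000 steps per day and a two-sided 95% interval based on z.

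- Half width = 1.96 × SD × √(2/n)
- n = 50 per arm: 1.96 × 2000 × √(2/50) = 784 (stated: about 800)
- n = 100 per arm: 1.96 × 2000 × √(2/100) = 554 (stated: 560)
- Reduction: 1 − 554/784 = 29% (stated: 30%)
- At the upper end of the stated SD range, n = 50: 1.96 × 3000 × √(2/50) = 1176

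The plan's figures reproduce. Time does not enter the formula, so correcting the time point changes none of them.

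**The case against.** The best defence is that the intended contrast can be inferred. The hypothesis is between arms, the primary outcome is fixed at week 24, the precision statement concerns a difference of two means, and the model runs to week 24. Few readers would conclude that the primary comparison is meant to be at week 12. This stands as an argument about intent, and it limits how serious the point is. It does not make the sentence correct: the difference carries an explicit time, and that time conflicts with the other sections. Nor is this detail that a condensed article leaves to a fuller document, because the article states a time point and states one that does not fit.

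The defence is also right that week-12 steps may exist, since daily steps are drawn from the device. A reader might infer that the 12-week difference cannot be estimated. The documents do not support that. What they lack is a scheduled assessment or a defined window at that time.

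A reader might also infer that success could be claimed at either time point, with an inflated type I error. No section allows that, and Primary Outcomes fixes a single endpoint. Nor is the 12-week difference the only inferential result planned: the article also plans mediation effects and complier average causal effect models. The full list of model terms may reasonably be left to a document not shown here.

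**Conclusion.** Wrong as written. The difference in step estimates is placed at 12 weeks, in conflict with the week 0 to week 24 primary outcome and the baseline and 6-month schedule. The between-arm difference that would answer the hypothesis at week 24 is not stated.

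The defect is confined to one sentence, but that sentence governs the primary comparison. It has no numerical size: sample size and precision are unchanged, and the documents support no error-rate figure.

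The conclusion rests on two readings: that the difference in question is between arms, which is the natural sense but is not spelled out, and that week 24 and 6 months are one occasion. If the difference were not between arms, the analysis section would state no between-arm step contrast at any time point, and the same correction would be needed.

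It would go too far to say that the plan cannot deliver the primary comparison. A model of change to week 24 can supply it. The text does not name it.

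**What to change.** Replace the sentence with one to this effect: the primary contrast is the MobileMen minus Stridekick difference in least-squares mean change in steps per day from baseline to week 24, reported with its standard error, 95% confidence interval and two-sided P value.

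Then either delete the 12-week reference or, if a week-12 comparison is intended, define the window of Fitbit days that supplies it and label that difference secondary. The reference to several postbaseline visits should be brought into line with whichever choice is made.

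The cost is one sentence, plus a window definition if week 12 is kept. No new data, visits or participants are needed. The correction should be dated and made before the outcome data are analysed.

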
The purpose of this paper is to describe the study protocol for examining the effectiveness of MobileMen. This trial will test the hypothesis that the MobileMen app will increase PA in African American men in comparison with Stridekick, a popular fitness app.

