### Participants

Eligibility criteria include self-identification as an African American male, a resting systolic blood pressure ≤159 mm Hg and a diastolic blood pressure ≤99 mm Hg (to reduce risk of exercise-induced cardiovascular events), free of significant medical problems that would impact their ability to engage in aerobic and/or resistance training, smartphone ownership, age > 30 years, and “low active” at baseline (defined as having an average daily accelerometer-assessed step count of <7500 steps) [61].

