### Recruitment and Screening

Community-based efforts, including advertising at churches, health fairs, Young Men’s Christian Association, fraternities, social media posts, and advertisements on paid, owned, and earned media, are being used to recruit study participants. Potential participants undergo a telephone screening to assess initial eligibility.

### Study Visit 1

Men who meet the initial inclusion criteria are invited for an in-person or remote orientation visit with study staff. Study staff review the study protocol and facilitate an informed consent process. During this study visit, participants complete several baseline assessments, including a sociodemographic questionnaire and height, weight, pulse, and resting blood pressure measurements. We calculate BMI by using self-reported weight and height (kg/m^2^). Health-related quality of life is assessed using the 36-item short-form health survey, a widely used validated measure with strong internal consistency (Cronbach α > 0.80 across most domains) and robust evidence of construct and criterion validity and has been validated in African Americans [62,63]. To assess PA and dietary habits, participants complete the International Physical Activity Questionnaire and National Cancer Institute’s Automated Self-Administered 24-hour Dietary Assessment Tool, respectively [64,65]. Self-efficacy for fruit and vegetable consumption is measured with 7 items that measure participants’ confidence in their ability to consume fruits and vegetables in different contexts like when away from home or in a rush [66]. Self-efficacy for PA is measured using the Self-Efficacy for Exercise Scale [67]. SDT-based motivation for PA is measured using the Behavioral Regulations in Exercise Questionnaire v.3 [68,69]. This 24-item questionnaire assesses the 6 SDT subtypes of motivation, with each item scored on a 5-point Likert scale ranging from 0 (not true for me) to 4 (very true for me). The Behavioral Regulations in Exercise Questionnaire v.3 has strong internal consistency for each motivational subscale; it validly measures the different types of motivation and is predictive of exercise behavior [68,69]. Eligible participants receive a Fitbit to wear for 1 week to assess baseline PA levels.

### Study Visit 2

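### Part of the app's evaluation rests on pre-post data with no between-arm contrast named; in men selected for low baseline steps, a within-arm rise could appear with no app effect

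*Protocol article*

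**What the plan says.** Three parts of the protocol article bear on this.

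- **Entry.** The Participants section requires men to be low active at baseline, "defined as having an average daily accelerometer-assessed step count of <7500 steps". Under Study Visit 1, "Eligible participants receive a Fitbit to wear for 1 week to assess baseline PA levels". Study Visit 2 checks wear compliance and gives a second activity criterion, by self-report: "Participants who self-report <60 minutes of moderate to vigorous PA on the International Physical Activity Questionnaire are eligible".
- **Outcome.** Under Primary Outcomes, the endpoint is the change in Fitbit steps from week 0 to week 24.
- **Analysis.** Under Statistical Analyses, a repeated-measures model is described, and "The step counts at baseline are included as a fixed factor in the model". The listed output, with standard errors, P values and 95% confidence intervals, is the least-squares mean change to week 24 and a difference in the estimates at 12 weeks. A later sentence adds: "The evaluation of the app will include its impact using the pre-post data". It names no comparator. The sentence after that looks at correlations and mean changes to see whether variables move alike in the two arms.

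**The concern.** A group chosen because its reading fell below a cut-off will, on average, read higher when measured again, because part of each low reading is temporary. If the week that applies the 7500-step limit is also the baseline for change, each arm's mean change contains this regression to the mean. Randomisation removes it from the difference between arms. It does not remove it from one arm's own change, and neither does adjustment for baseline steps, because a least-squares mean change is still evaluated in the selected men.

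The text leaves that contaminated quantity available as evidence of impact. Taken literally, the week-24 P value attaches to change from baseline, and the only difference named is not at the primary time point. If the between-arm result were inconclusive, a significant rise within the MobileMen arm could be reported as impact although neither app had changed anything.

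**Working it through.** **The plan's own precision figure.** The Sample Size and Power Calculation section gives 50 men per arm, an SD of 2000 and a two-sided 95% interval based on z. The half-width is 1.96 × 2000 × √(2/50) = 784 steps per day, against a stated value of about 800. With the sample doubled it is 1.96 × 2000 × √(2/100) = 554, against a stated 560. Both reproduce. With an SD of 3000 and 50 per arm it is 1176. These figures are not in dispute; they give a yardstick.

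**Inputs for the selection effect.**
- Cut-off c = 7500 steps (Participants).
- SD 2000 to 3000 (Sample Size and Power Calculation), taken as the SD in the population from which men are selected.
- Population mean μ of 6000 to 8000: an assumption, not in the document.
- Correlation ρ between the week-0 and week-24 readings of 0.6 to 0.9: an assumption, not in the document.
- Bivariate normal readings, equal SD at both times, no effect of either app.

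**Formula.** With a = (c − μ)/SD, the expected change in selected men is (1 − ρ) × SD × φ(a)/Φ(a), where φ and Φ are the standard normal density and distribution function.

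**Worked example.** For μ = 7000 and SD = 2000, a = 500/2000 = 0.25 and φ(a)/Φ(a) = 0.3867/0.5987 = 0.646. Selected men average about 1292 steps below the population mean. With ρ = 0.7 the expected rise is 0.3 × 1292 = 388 steps per day.

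**Expected rise in one arm, no app effect (steps per day).**

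| μ | SD | ρ = 0.6 | 0.7 | 0.8 | 0.9 |
|---|---|---|---|---|---|
| 6000 | 2000 | 312 | 234 | 156 | 78 |
| 7000 | 2000 | 517 | 388 | 258 | 129 |
| 8000 | 2000 | 771 | 578 | 385 | 193 |
| 6000 | 3000 | 611 | 458 | 305 | 153 |
| 7000 | 3000 | 834 | 625 | 417 | 208 |
| 8000 | 3000 | 1088 | 816 | 544 | 272 |

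The range is 78 to 1088. At μ = 7000 and ρ = 0.7, the rise is about half the between-arm half-width at the same SD: 388/784 = 0.49 and 625/1176 = 0.53.

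**Consequence for tests.** Each scenario was simulated 4000 times with 50 men per arm, complete follow-up and no app effect. The one-arm column counts a significant increase on a two-sided 5% paired t test, for which the nominal rate in that direction is 2.5%. The between-arm column is an analysis of covariance on baseline steps, two-sided at 5%.

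| μ | SD | ρ | One-arm false increase | Between-arm rejection |
|---|---|---|---|---|
| 6000 | 2000 | 0.9 | 9% | 5.0% |
| 7000 | 2000 | 0.8 | 31% | 4.7% |
| 7000 | 2000 | 0.7 | 45% | 5.1% |
| 7000 | 3000 | 0.7 | 50% | 4.9% |
| 7500 | 3000 | 0.7 | 62% | 4.9% |

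The simulated between-arm estimate lay within 9 steps of zero in every scenario.

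**The case against.** The trial is comparative throughout. The Introduction states the hypothesis that "the MobileMen app will increase PA in African American men in comparison with Stridekick"; men under one entry rule are randomised to the two apps; the precision calculation is for a difference of two means; and baseline steps are in the model. The quoted sentence says only that the evaluation will include pre-post data. Elsewhere the article uses pre- and postintervention as labels for its two measurement occasions, so the phrase is compatible with comparing changes between arms, and the following sentence does look at both arms. No one-arm test is named as support for an efficacy claim.

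All of that stands, and it limits the point. A reader might infer that the app's impact will be decided on uncontrolled change, and that regression to the mean is bound to pass for an app effect. The documents do not support that: it happens only if the within-arm reading is chosen.

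Two further limits stand. That one week serves for both selection and baseline is an inference. It is well supported, since no other device measurement before randomisation is described, but Study Visit 2 itself mentions only wear compliance and the questionnaire. The size also depends on a mean and a correlation that the documents do not give. Telephone screening and the self-report criterion could lower the mean of men reaching the Fitbit week, which moves the answer towards the low end.

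What the objection does not remove is the ambiguity. The article makes this statement itself, so it is not a detail left to an analysis plan, and nothing in the section says that week-24 impact means the difference between arms.

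**Conclusion.** The point holds as a matter of wording with a real consequence. The plan describes an impact evaluation from pre-post data without naming a between-arm contrast, and it attaches week-24 P values to change from baseline while naming a difference only at 12 weeks. A within-arm reading could show an increase with no app effect: about 80 to 1090 steps per day over the assumed ranges, and a false increase in roughly 9% to 62% of trials in the scenarios simulated. This rests on the same-week inference, the assumed mean and correlation, and normality. The randomised, baseline-adjusted comparison is sound, with about 5% rejection under no effect. Clarifying the text is a cheap improvement, not a correction of a failed design.

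**What to change.** - State that the impact of MobileMen is assessed by the between-arm, baseline-adjusted difference in change in steps at week 24, and name that contrast in the sentence listing the model output.
- Report each arm's own change descriptively, with a confidence interval and no P value, and note that selection on baseline steps inflates it.
- Reword the pre-post sentence to match.

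This takes a few sentences and no new data, visits or participants. The one downside is that within-arm P values are given up.

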To address the gap in mHealth apps developed specifically for African American men, we developed, to the best of our knowledge, a first of its kind smartphone app, MobileMen, to support PA engagement in this population. The process for developing this app and the further rationale for the selected components are described elsewhere [40]. MobileMen is grounded in 2 behavior change theories: social cognitive theory (SCT) and self-determination theory (SDT). SCT states that the environment and a person’s behavior interact to shape behavior and that self-efficacy is the key component to behavior change [41]. SCT was the foundation of the PA adoption content focusing on self-monitoring, goal setting, and social support in the MobileMen app. We chose SCT because SCT-grounded interventions have been effective at increasing and maintaining PA in African Americans [42-47]. In addition, SDT posits that satisfying 3 fundamental needs contributes to behavior change: perceived competence, a feeling of relatedness (feeling connected to others), and autonomy (feeling that change is a choice and not coerced) [48-52]. When an activity fulfills these 3 needs, people can become more autonomously motivated, resulting in more PA initiation and persistence [53]. In African American men, specifically, intrinsic motivation associates PA engagement with personal values and overall health goals, increasing the likelihood that they will persist with the behavior [54]. In the MobileMen app, we included features such as reminders and goal setting to support the development of autonomy [55]. To support competence, we included activity history and feedback such as cumulative exercise statistics aggregated over weeks and months, logging of weight training workouts and health metrics, and tangible and digital rewards [55]. We also included the ability to participate in competitions with other users and a message function to support the basic need of relatedness [55].

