### MobileMen App

MobileMen is a mobile app tailored to the needs of African American men who aspire to increase their PA engagement [60]. MobileMen was developed using an extensive and iterative process described elsewhere [40]. The development of the MobileMen app was completed in July 2024 and is available for use on both iOS and Android platforms. See Table 1 for features of the MobileMen app.

**Table 1 table1:** Features of the MobileMen and Stridekick apps.

Feature	MobileMen app	Stridekick app
Syncs to Fitbit device	✔	✔
Display physical activity data	✔	✔
Message boards	✔^a^	✔
Goal setting	✔	✔
Challenges	✔	✔
Educational content (physical activity, nutrition, and behavior change articles)	✔	N/A^b^
Allows tracking of health metrics (blood pressure, blood glucose, body weight, and cholesterol)	✔	N/A
Incentives (virtual badges and tangible prizes)	✔	✔^c^
Designed with a behavior change theory framework	✔	N/A
Designed specifically for African American men	✔	N/A

^a^MobileMen is utilizing a private Facebook group for the message board feature during the comparative effectiveness trial.

^b^N/A: not applicable.

^c^Stridekick offers virtual badges but not tangible prizes.

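### App-use intensity, which enters the complier models, is measured partly by badges and incentives that are earned for physical activity

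*Protocol article*

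**What the plan says.** The last paragraph of Statistical Analyses in the Protocol article sets out how acceptability and intensity of interaction with MobileMen will be examined. The criteria are open-ended. They begin with logins and notifications and continue with "number of activities inputted, badges earned, tips read, number of health parameters inputted, competitions competed in, and incentives earned". The next sentence reads: "Complier average causal effect models will be used to examine the intensity of the intervention app utilization".

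Three other places bear on what those criteria measure:

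- **Abstract, Methods:** the app's features include "digital badges earned for PA; tangible prizes like exercise equipment".
- **Table 1, under MobileMen App:** one row is "Incentives (virtual badges and tangible prizes", so incentives include badges. Another row is "Syncs to Fitbit device".
- **Primary Outcomes:** the primary outcome is the change in Fitbit step count from week 0 to week 24.

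On activities inputted, the Introduction describes "logging of weight training workouts and health metrics" as an app feature, which reads as entry by the user.

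**The concern.** A measure of exposure to an intervention should record what the man did with the intervention. Badges are awarded for physical activity, so a badge count records at least in part how active he was. The same holds for incentives to the extent that they consist of badges. Both are nevertheless named as measures of use, on the same footing as logins and tips read.

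Two results are exposed. First, any descriptive comparison of heavier with lighter users would tend to show more steps among heavier users, even if engagement did nothing, because activity is on both sides of the comparison. Second, in the complier models, men who become more active for any reason could be classed as compliers, while men who log in and read but do not walk more could be classed as non-compliers. The Conclusions say that the trial is to inform app modifications before a large-scale effectiveness trial, so a contaminated measure of use could mislead the next step. The problem would remain with any comparator app.

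**Working it through.** The plan gives no figure on this point, so there is none to reproduce. The check has a textual part and two illustrations.

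**Sorting the criteria.** Counting notifications sent and received as one, eight criteria are named.

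- *Badges earned:* earned for physical activity, stated in the Abstract.
- *Incentives earned:* include badges (Table 1). The rule for earning tangible prizes is not given.
- *Activities inputted:* a user entry, but a more active man has more to enter.
- *Logins, tips read, health parameters inputted:* actions in the app that do not require physical activity.
- *Notifications, competitions:* the article does not say enough to place them.

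Two of the eight are thus wholly or partly driven by activity, and a third is mixed.

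**Illustration 1: descriptive association.** Assume an equal-weight score of m = 8 standardised items. Let k of them each correlate r with steps, and be otherwise independent. Let the other m − k items be unrelated to steps and correlate c with each other. Then

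corr(score, steps) = k·r / √[m + k(k−1)r² + (m−k)(m−k−1)c].

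The values r = 0.5 to 0.8 and c = 0 or 0.5 are assumptions.

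| k | c | r = 0.5 | r = 0.8 |
|---|---|---|---|
| 2 | 0 | 1.0/√8.5 = 0.34 | 1.6/√9.28 = 0.53 |
| 2 | 0.5 | 1.0/√23.5 = 0.21 | 1.6/√24.28 = 0.32 |
| 3 | 0 | 1.5/√9.5 = 0.49 | 2.4/√11.84 = 0.70 |
| 3 | 0.5 | 1.5/√19.5 = 0.34 | 2.4/√21.84 = 0.51 |

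The true value is 0 throughout, and the formula returns 0 when k = 0. The rows with c = 0.5 are the more realistic, since logins, tips and entries by the same man will go together. The rows with k = 3 treat activities inputted as if it were a badge, which the wording does not support; they are shown only as an outer bound.

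**Illustration 2: complier effect.** The standard estimate is the intention-to-treat effect divided by the proportion of compliers. Assume that half the men truly use the app, that use adds 1000 steps/day, and that step change has an SD of 2000. (The article assumes that SD for steps per day in its sample size section.) The intention-to-treat effect is 0.5 × 1000 = 500.

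- Compliance defined by true use: 500/0.5 = 1000, which is correct.
- Compliance defined by badges alone, with a badge awarded for a step change above a threshold (simulated; the simulated intention-to-treat effect was about 499):

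| Threshold (steps/day) | Labelled compliers | Estimate | True mean effect in labelled compliers | True mean effect in labelled non-compliers |
|---|---|---|---|---|
| −1000 | 0.768 | 650 | 548 | 338 |
| 0 | 0.596 | 838 | 579 | 381 |
| 500 | 0.500 | 998 | 598 | 401 |
| 1000 | 0.405 | 1234 | 617 | 419 |
| 1500 | 0.314 | 1591 | 639 | 435 |

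The estimate moves with the threshold and never equals the mean effect in the men it is said to describe. The labelled non-compliers also show an effect, which breaks the exclusion restriction on which the method rests. If assignment has no effect, the numerator is 0 and so is the expected estimate, whatever the label.

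**The case against.** The strongest reply is that the article defines no score. It lists criteria, names a class of model, and does not say which criterion, weight or threshold makes a man a complier. That detail may sit in a full protocol or analysis plan that is not shown, and a login-based rule would be compatible with the text. This stands as a limit on any magnitude. It does not remove the point, because badges and incentives are expressly named as measures of intensity and the next sentence carries intensity into the complier models without restriction.

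A reader might infer more than the article supports:

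- *That the complier models would produce an effect where none exists.* In the standard form they would not, as shown above. Only a descriptive comparison of use with steps is exposed to that error.
- *That men who have stopped using the app would still be counted as users.* This needs badges to accrue through the Fitbit sync without the app being opened. That is plausible but nowhere stated. The circularity does not need it: among men who all keep using the app, the more active still earn more badges.
- *That activities inputted is merely a by-product of the outcome.* It reads as an action in the app, and the example given, weight training, is not stepping.
- *That the planned examination of noncompliant men uses this list.* The article does not tie the two together.

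**Conclusion.** The point holds for badges, and for incentives in so far as they include badges: part of the stated measure of use is produced by the behaviour under evaluation. If these items enter the measure, the direction is clear for descriptive comparisons, where use and steps will look more closely linked than they are. For the complier models the harm is an effect of the wrong size, attributed to the wrong men, when a true effect exists; the error can go either way.

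The sizes are illustrative: correlations of 0.21 to 0.53 with two activity-driven items, and complier estimates of 650 to 1591 against a true 1000 steps/day in the extreme case of compliance defined by badges alone. They rest on assumed weights, item correlations and a badge rule, none of which the article gives. The analysis concerned is a supporting one, and the primary comparison of randomized arms is untouched.

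**What to change.** In the app-utilization paragraph of Statistical Analyses, state that use intensity and complier status for the complier models are defined only from logged app actions that do not require physical activity. Three are already on the list: logins, tips read and health parameters inputted. State that badges and incentives are reported descriptively and do not enter those models. Report activities inputted separately, since it is a user entry that also rises with activity. Notifications and competitions should count only if the way the app generates them shows that they do not depend on activity. Fix the rule before the utilization data are analysed.

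The cost is a change of wording, as the items to be kept are already planned for collection. The downside is a measure of use with fewer components.
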